#### Primary Outcome Measures:

Primary outcomes will be assessed at baseline, post three months, and post six months in all participants. A revised Client Satisfaction Questionnaire (CSQ-8-R) will be administered and contains questions investigating the quality of the intervention, satisfaction with the intervention, if the intervention has helped connect the participant with other resources, and more. A modified Genetic Alliance, “Does it Run in the Family” assessment will also be administered. This measure has items such as: “The toolkit made our conversations with family better; toolkit has encouraged me to talk to my own family about family health history.”^67^

#### Secondary Outcome Measures:

Secondary outcomes will also be assessed at baseline, post 3 months, and post 6 months in all participants. Comprehension of the FHH tool will be assessed using a subscale from the Functional Health Literacy Scale such as: print too small, content was difficult to read, etc. Number of screenings requested, and number of screenings received will both be assessed using a modification to the Family Health Communication Quotient (FHCQ). This measure will also be used to assess the number of screenings requested and received in the 6 months prior to baseline.

Health literacy will be assessed using subscales of the Health Literacy Questionnaire (HLQ) Communicative and Critical Health Literacy Scale (CCHL).^69^ Comprised of nine independent scales, the HLQ was modified to assess understanding of health information and use of that information to make health-related decisions.^69,70^ Health communication will be determined using the HLQ scale to assess the ability to actively engage providers and support (family) which assesses the ability to communicate thoughts about one’s health.^69,70^ The Family Health Communication Quotient (FHCQ) will be used as a secondary measure of health communication. The FHCQ measures a general orientation toward discussion about health between family members, frequency and effects of discussions, communication style when discussing health, and attitudes toward health practices.^68,71^ It will ultimately be used to analyze the length and meaningfulness of discussions with family members.

### Analytic Plan

#### Data Analysis:

To achieve the goal of understanding the assessment and feasibility of this intervention, study recruitment and refusal rates, participants’ willingness to be randomized, follow-up rates, reliability, range of responses to study questionnaires, and success of the interventionist training program will be examined. The feasibility and acceptability of AAFHHEP and EFHHEP, as described previously, will be summarized with descriptive statistics. The acceptability of both interventions using data from CSQ-8-R satisfaction questionnaire and detailed exit interviews will be examined. Internal consistency and interrater reliability of fidelity scales will be computed

Primary RCT analyses will be intent-to-treat (using data from all enrollees as randomized) for the outcomes of FHH use (FHH discussed with a family and health care provider). Secondary dose- response analyses within intervention group evaluating effects of receiving 0, 1, or 2 intervention sessions will also be conducted. Longitudinal data will be analyzed using linear mixed effects or generalized linear mixed effects models with the appropriate error distribution (e.g., Binary) and covariance adjustment for the baseline version of the outcome where possible. These models can accommodate data missing at random and will be used to estimate the effect sizes at 3 and 6-month time points.

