**Methods:**

The proposed sample will be composed of 195 African American adults ages 18 + who live in Genesee County, Michigan. The study consists of two phases: the development phase and the randomized pilot study phase. The goal of the development phase (n = 95) is to explore how Family Health History toolkits can be modified to better serve the African American community using a community based participatory research approach and to create a culturally tailored family health history toolkit. In the pilot study phase, 100 participants will be randomized to the culturally tailored toolkit or the current standard Family Health History toolkit. Outcomes will include feasibility and acceptability of the intervention.

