#### Recruitment and Enrollment

Participant recruitment strategies will include flyers, public service announcements, and partnerships with the Community Based Organization Partners (CBOP), the Genesee County Health Department (GCHD), and other Michigan State University-based community councils, action boards, resident consortiums, and advisory groups. These methods were already conducted for the development phase and will continue for the pilot study phase. Potential participants will reach out directly to the study via phone and a research assistant will contact them. Once the person arrives to the scheduled focus group, workshop, open trial session, or randomized control trial session, they will be consented into the study by a research assistant.

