The final part of the development phase is the open trial. This component consists of 15 AA adults that meet the aforementioned eligibility criteria. The open trial provides the opportunity to refine the created FHH toolkit. Study participants will fill out a session evaluation form asking them about their opinions of each session and how sessions could be made more helpful. Participants will also complete an intervention-specific End-of-Intervention Questionnaire, which addresses their perceptions of the helpfulness of each intervention component and their comfort with research procedures such as audiotaping and timing of the two FHH sessions. Participants will discuss their responses at an exit interview with the study principal investigator to aid in manual revisions.

The pilot study phase consists of the RCT. During the RCT, the intervention group will receive the AAFHHEP while the control group receives the EFHHEP. A total of 100 participants over the course of seven months will be recruited for this portion of the study. AAFHHEP participants will receive the intervention in two 60–90-minute sessions about 2 weeks apart. Session 1 focuses on understanding and reviewing FHH tools and its utility in risk assessment, including the AAFHHEP toolkit. Session 2 addresses family engagement strategies and provider engagement strategies. This session helps participants to develop personalized engagement plan resulting to actively engage family and their primary care providers (PCPs) utilizing the AAFHHEP toolkit. This toolkit will tailor messages around culture and spirituality that may preclude individuals from communicating. Participants will discuss what an FHH is, how choices affect health, how genetics affect health, what information to collect, how to engage family members in the conversation, how to organize FHH, and how to share information with their PCP. The feasibility and acceptability of AAFHHEP and EFHHEP will be assessed by examining rates of treatment attendance, rates of treatment completion (attending both scheduled group sessions) and drop-out, and scores on the End of Treatment Questionnaire, described below.

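### The within-arm dose-response analysis is worded as evaluating effects of sessions, but the number attended is not randomised, so a gradient can arise from who attends

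*Protocol article*

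**What the plan says.** - **The analysis.** Under Data Analysis, the protocol article states that secondary dose-response analyses "within intervention group evaluating effects of receiving 0, 1, or 2 intervention sessions will also be conducted".
- **What is randomised.** The abstract's Methods paragraph says that "100 participants will be randomized to the culturally tailored toolkit or the current standard Family Health History toolkit". Nothing in the article allocates participants to a number of sessions.
- **The scheduled dose.** Under Procedures, "AAFHHEP participants will receive the intervention in two 60–90-minute sessions about 2 weeks apart". Receiving 0 or 1 is therefore a departure from the schedule. The same section treats attendance as a feasibility outcome, through "rates of treatment completion (attending both scheduled group sessions) and drop-out".
- **Adjustment.** The sentence after the dose-response sentence specifies mixed models with "covariance adjustment for the baseline version of the outcome where possible". Under Primary and Secondary Outcomes, baseline FHCQ orientation and prior physician discussions are named as covariates, but for tests between conditions. No predictor of attendance is named for the dose-response analysis.
- **Status.** "Primary RCT analyses will be intent-to-treat (using data from all enrollees as randomized) for the outcomes of FHH use". The dose-response analysis is secondary to this.

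**The concern.** A comparison of participants by sessions attended, inside one arm, has no randomised contrast behind it. People who come twice may differ from those who come once or not at all in motivation, free time, health literacy or how readily their family talks about health. The main outcome is whether the participant discussed FHH with family and with a provider, and the same traits could plausibly drive that. The article itself proposes health literacy and health communication as mechanisms.

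Wording the result as effects of receiving sessions invites a causal reading that the design does not support. In a pilot whose stated emphasis is estimation, a confounded point estimate can mislead whether or not it reaches significance.

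**Working it through.** **1. The plan's own figure.** No precision or power is stated for the dose-response analysis. The one power statement (Sample Size Adequacy) covers the comparison between arms, with about 40 followed per arm, alpha .05 (taken as two-sided), and d = .63 or 80% vs. 50%.

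- Continuous: Φ(0.63 × √(40/2) − 1.96) = Φ(2.817 − 1.960) = Φ(0.857) = 0.80. The exact t-test gives 0.795.
- Binary: Φ([0.30 × √40 − 1.96 × √(2 × 0.65 × 0.35)] / √(0.80 × 0.20 + 0.50 × 0.50)) = Φ((1.897 − 1.322)/0.640) = Φ(0.899) = 0.82.

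The claim of at least .80 reproduces, but it says nothing about the within-arm comparison.

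**2. Gradient from selection alone (large sample, unadjusted).** These inputs are assumptions, not document figures:

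- Attendance of 10%, 15% and 75% at 0, 1 and 2 sessions.
- An 80% overall discussion rate. The article uses 80% only as one side of its power contrast.
- No session effect.
- Attendance and discussion as thresholds on two standard normal variables with correlation r.

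The rate in each attendance group is P(discuss and group)/P(group) from the bivariate normal distribution.

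| r | 0 sessions | 1 session | 2 sessions | OR, 2 vs 0 |
|---|---|---|---|---|
| 0 | 0.800 | 0.800 | 0.800 | 1.0 |
| 0.1 | 0.748 | 0.773 | 0.812 | 1.5 |
| 0.2 | 0.691 | 0.747 | 0.825 | 2.1 |
| 0.3 | 0.629 | 0.720 | 0.839 | 3.1 |

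For r = 0.3: (0.839/0.161)/(0.629/0.371) = 5.21/1.70 = 3.1. With a 50% discussion rate the odds ratios at r = 0.2 and 0.3 are 2.0 and 3.0, so the result depends little on prevalence.

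**3. With baseline adjustment, at the trial's size.** A second model simulated the intervention arm with 50 randomised (40/0.8), 20% lost at random, and inert sessions. Attendance was assumed to be 10/20/70%. A latent trait drives both attendance (correlation g) and outcome (log-odds b per SD). A logistic model at one time point regresses outcome on sessions, adjusted for a baseline covariate that correlates ρ with the trait. Each row used 1,500 simulated trials.

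| Selection (g, b) | ρ | Large-sample OR per session | OR, 2 vs 0 (squared) | Share with p < .05 |
|---|---|---|---|---|
| none (0, 1.0) | 0 | 1.00 | 1.0 | 2% |
| weak (0.3, 0.7) | 0 | 1.21 | 1.5 | 6% |
| weak | 0.8 | 1.12 | 1.2 | 4% |
| moderate (0.5, 1.0) | 0 | 1.69 | 2.9 | 12% |
| moderate | 0.8 | 1.23 | 1.5 | 4% |
| strong (0.7, 1.5) | 0 | 2.70 | 7.3 | 38% |
| strong | 0.8 | 1.68 | 2.8 | 8% |

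An informative baseline covariate shrinks the bias but does not remove it. This model has one time point, not the planned longitudinal mixed model.

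**4. Precision.** With 40 followed and the split in step 2, the cells hold 4, 6 and 30 people. For 2 vs 0 at r = 0.3, SE(log OR) = √[1/(4 × 0.629) + 1/(4 × 0.371) + 1/(30 × 0.839) + 1/(30 × 0.161)] = √1.318 = 1.15. The interval is exp(1.125 ± 1.96 × 1.15), about 0.3 to 29. Under Recruitment and Enrollment, when people arrive at their scheduled session "they will be consented into the study by a research assistant", so the 0-session group may be smaller still. The article does not state when randomisation occurs, so this is an inference.

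**5. Combining 0 and 1.** At r = 0.3 the combined rate is (0.10 × 0.629 + 0.15 × 0.720)/0.25 = 0.684, and the OR for 2 vs 0 or 1 is (0.839/0.161)/(0.684/0.316) = 2.4. Combining helps with sparse cells, not with confounding.

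**The case against.** The strongest reply is that this is one sentence about a secondary analysis in a condensed article. Covariates, sparse cells and caveats normally sit in the full protocol or SAP, which are not shown. That stands for those details, and their absence is not the point. What the article does fix is the contrast and its description as effects.

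Three stronger readings are tempting, and the documents support none of them.

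- **That the analysis is bound to show an effect.** There is no bias if attendance is unrelated to prognosis, and the odds ratios in step 2 are unadjusted, large-sample and assumption-based. In samples of 40 under the same scenario, a significant positive gradient appears in about 19%, 11% and 6% of trials at r = 0.3, 0.2 and 0.1. Rare significance is only partial reassurance, because the point estimate is biased either way.
- **That the result will set the number of sessions in the later trial.** The article links the later trial to the proposed mediators and nowhere to the dose result.
- **That an arm-by-sessions interaction would settle the matter.** Completion is recorded in both arms, so the comparison is possible. With about 80 followed, and about 16 non-discussers at an 80% rate, it would be very imprecise. Nor is it a clean check: attendance is post-randomisation in both arms, and a tailored programme may change who attends.

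**Conclusion.** The point holds as a wrong causal label on a non-randomised comparison. Inert sessions can produce a gradient, and the stated adjustment reduces confounding without guaranteeing its removal. The illustrative size is an unadjusted OR for 2 versus 0 sessions of about 1.5 to 3.1, for assumed latent correlations of 0.1 to 0.3 and an assumed 10/15/75% attendance split. It is 1.0 when attendance and prognosis are unrelated. The actual attendance pattern and strength of selection cannot be known from the article. The intent-to-treat comparison, the power statement and the feasibility aims are unaffected. The change is worth making but does not bear on the trial's main conclusions.

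**What to change.** - Describe the comparison by sessions attended as an exploratory association, and drop the reference to effects.
- Adjust for baseline predictors of attendance that the trial already collects, such as FHCQ and HLQ scores, education and prior physician discussions. Keep the set small, since about 40 people are followed in the arm.
- Combine 0 and 1 sessions if the 0 group is nearly empty.
- Optionally show the attendance gradient in the control arm alongside, descriptively and without a formal interaction claim.

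The cost is a weaker claim and slightly more analysis work. No new data, sample size change or change to the primary analysis is needed. Residual confounding will remain and should be acknowledged in the report.

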#### Primary and Secondary Outcomes:

Odds ratios and 95% confidence intervals for discussing the FHH with family and discussing the FHH with a physician (separately) will be calculated. For discussing the FHH with family, exploratory tests for differences between conditions will use GLME, with baseline FHCQ scores that assess the family’s general orientation toward health discussions as a covariate. With regards to discussing the FHH with a physician, exploratory tests for differences between conditions will use GLME with binary errors with the baseline number of past 6-month discussions with a physician as a covariate. For participants who discussed the FHH with family, effect size (Cohen’s d) and 95% confidence intervals for self-reported length of FHH discussion with family and meaningfulness of discussion with family will be calculated.

To explore secondary outcome measures, we will use separate HLM analyses to calculate effect size (Cohen’s d) and 95% confidence intervals for satisfaction with and for understandability of the FHH intervention at Month 3 and Month 6. Effect sizes and 95% confidence intervals for arm differences in the number of screenings requested and number of screenings received across 3- and 6-month follow-ups will also be calculated. Effect sizes (Cohen’s d) and 95% confidence intervals for between-arm differences will be calculated for health literacy (HLQ scores) and for health communication (HLQ scores; FHCQ scores) at 3 and 6 months.

Although this intervention development study is not formally powered to test mediation, Preacher and Hayes approach^74^ will be used to explore whether health literacy and/or health communication appear to be reasonable to test as mechanisms of the effects of the culturally adapted FHH (relative to the standard FHH) on number of health screenings received, in a larger trial. Sex and age as potential moderators of intervention effects will be explored.

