#### Sample Size Adequacy:

The primary purpose of this pilot study is to develop the intervention and test feasibility/acceptability of interventions and research procedures as well as preliminary efficacy of the intervention. In the RCT, with follow-up data from 80 participants in intent to treat analyses (about 40 per condition, after the projected 20% attrition before month 3), we will have statistical power adequate (> = .80) to detect medium to large effects (Cohen’s d = .63 for continuous outcomes; 80% vs. 50% for dichotomous outcomes) with alpha of .05. The primary emphasis will be on estimating the effect for differences between conditions.

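### Length and meaningfulness of family discussion are compared only among participants who had one, a subset formed after randomisation, so the planned Cohen's d is not a randomised estimate of the intervention effect

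*Protocol article*

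**What the plan says.** The protocol article, Analytic Plan, Primary and Secondary Outcomes, begins with the two yes/no outcomes: "Odds ratios and 95% confidence intervals for discussing the FHH with family and discussing the FHH with a physician (separately) will be calculated". It then turns to how long and how meaningful the family discussions were. The sentence opens "For participants who discussed the FHH with family, effect size", and it says that d and its 95% confidence interval for "self-reported length of FHH discussion with family and meaningfulness of discussion with family will be calculated".

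Three other places bear on this:

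- Data Analysis makes discussing the FHH an efficacy outcome. It says "Primary RCT analyses will be intent-to-treat (using data from all enrollees as randomized", and that this is "for the outcomes of FHH use (FHH discussed with a family and health care provider".
- Procedures shows that the intervention aims at this behaviour: "Session 2 addresses family engagement strategies and provider engagement strategies".
- Sample Size Adequacy assumes follow-up on 80 participants, about 40 per arm. It gives d = .63 for continuous outcomes and "80% vs. 50% for dichotomous outcomes" as the differences detectable with power of at least .80.

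The article gives no all-participant version of the length and meaningfulness comparison. It also does not label the discussers-only result as descriptive.

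**The concern.** Randomisation makes the arms comparable as assigned. It does not make comparable two subsets picked out by something that happens later and that the assignment may influence. If the tailored toolkit prompts conversations in people who would not have had one with the standard toolkit, the tailored arm's discussers include those less inclined people and the control arm's discussers do not. A difference in length or meaningfulness may then reflect who is in each subset, not what the toolkit did to the conversations.

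The methods named elsewhere in the article do not repair this. The mixed models in Data Analysis accommodate data missing at random, but for someone who had no discussion its length is undefined, not missing. The baseline FHCQ covariate is named for the yes/no discussion model, not for these two outcomes.

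At stake is the meaning of two effect sizes in a pilot whose stated emphasis is on estimating differences between conditions. In the plausible case where readier talkers have longer or more meaningful talks, a toolkit that succeeds in starting conversations would look worse on their quality than it is.

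**Working it through.** **1. The plan's own power figure.** Inputs from Sample Size Adequacy: 40 per arm, d = 0.63, 80% vs 50%, alpha .05 (taken as two-sided; the article does not say). "100 participants will be randomized to the culturally tailored toolkit or the current standard Family Health History toolkit", and 100 × 0.80 = 80.

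- Continuous, normal approximation: d × √(n/2) = 0.63 × √20 = 2.817; 2.817 − 1.960 = 0.857; power = 0.804. The noncentral t gives 0.795.
- Dichotomous, normal approximation: power 0.816 with 40 per arm.

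The stated figure reproduces.

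**2. Size of the subset.** Assumption: the 80% and 50% apply to family discussion, with the tailored arm higher. Then 40 × 0.80 = 32 and 40 × 0.50 = 20 participants contribute.

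**3. Expected d when there is no true effect.** Model (an assumption): each participant has a standard normal readiness to discuss, and a standard normal length or meaningfulness correlated r with it. The arm has no effect on length or meaningfulness. A participant is in the subset if readiness exceeds c, where c is set so that the proportion p discusses. With λ = φ(c)/p:

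- mean outcome among discussers = r × λ
- variance among discussers = 1 − r² × λ × (λ − c)

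For p = 0.80: c = −0.842, λ = 0.350, λ(λ − c) = 0.417. For p = 0.50: c = 0, λ = 0.798, λ(λ − c) = 0.637.

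With r = 0.3:

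- difference in means = 0.3 × (0.350 − 0.798) = −0.134
- variances = 0.962 and 0.943; pooled SD = √[(31 × 0.962 + 19 × 0.943)/50] = 0.977
- d = −0.134/0.977 = **−0.14**

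The same steps for other values of r, and for a smaller difference in discussion rates, give:

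| Assumed r | d at 80% vs 50% | d at 65% vs 50% |
|---|---|---|
| −0.3 | +0.14 | +0.07 |
| 0 | 0.00 | 0.00 |
| 0.1 | −0.05 | −0.02 |
| 0.3 | −0.14 | −0.07 |
| 0.5 | −0.24 | −0.12 |
| 0.7 | −0.36 | −0.19 |

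With equal discussion rates d is 0 in this model, because the model then selects the same kind of person in both arms.

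**4. Precision.** Near d = 0, the standard error of d is √(1/n₁ + 1/n₂).

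- 32 vs 20: √(0.03125 + 0.05) = 0.285; 95% half-width 0.56
- 40 vs 40: √0.05 = 0.224; 95% half-width 0.44

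Power for d = 0.63 with 32 vs 20 is about 0.58 (noncentral t; 0.60 by normal approximation). The d detectable with 80% power is about 0.81.

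**The case against.** The strongest reply is that this is a peripheral analysis. Project Overview calls feasibility and acceptability the ultimate analytical goal. The odds ratio for discussing with family is analysed as randomised and is untouched. Between-arm effect sizes for health communication (HLQ and FHCQ) are planned at 3 and 6 months, so the discussers-only d is not the only evidence on communication. The sentence plans no test, and a spurious −0.14 or −0.24 is small beside a half-width of 0.56. All of this stands and limits the severity. It does not remove the fault, because a confidence interval shows sampling error and not selection.

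It can also be said that the sentence does not mention arms. That is true. A between-arm reading is still the natural one: Cohen's d is used for arm differences in the paragraphs that follow, and Sample Size Adequacy puts the emphasis on differences between conditions.

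A reader might infer three stronger things that the article does not support:

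- *That d is certain to be biased against the tailored toolkit.* Sign and size depend on a correlation the article does not give. They also depend on discussion rates it does not forecast: the 80% vs 50% is a detectable difference for dichotomous outcomes in general.
- *That the power statement is wrong or contradicted.* It refers to follow-up data from 80 participants in intent-to-treat analyses and makes no claim for the subset.
- *That this d will drive the larger trial.* The article links that trial to the proposed mediators, health literacy and health communication, and not to this estimate.

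**Conclusion.** The point holds in conditional form. The article commits to an effect size in a group defined after randomisation by an outcome the intervention targets, so the comparison lacks the protection of randomisation. It is biased as an intervention effect when two conditions both hold: the arms differ in who discusses, and readiness to discuss is related to length or meaningfulness. Under the assumed 80% vs 50% and no true effect, the spurious d is about −0.14 to −0.24 for correlations of 0.3 to 0.5. It shrinks with closer discussion rates, vanishes at no correlation and changes sign at a negative one. The loss of precision, from about 40 vs 40 to about 32 vs 20, rests on the same assumed rates. Severity is moderate.

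**What to change.** Make the between-arm comparison on all participants with follow-up, in the arm to which they were randomised.

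- *Length:* set to 0 minutes when there was no discussion. Use a rank-based or ordinal analysis, or a two-part model summarised as one overall contrast (in each arm, proportion discussing × mean length among discussers). The second part of a two-part model must not be reported alone as the effect, because it carries the same selection.
- *Meaningfulness:* analyse as an ordered outcome with no discussion as the lowest category.
- *Discussers only:* keep the summaries by arm, labelled as descriptive and not as an intervention effect.

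The cost is a few lines of analysis text and a little code, with no extra participants or data. The small downside is that the all-participant estimate combines whether people talked with how much or how well they talked. Reporting it beside the planned odds ratio for discussing and the descriptive discussers-only summaries lets the reader see both components.
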